#### Repeated Measurements Over Time

Each subject is assumed to have his or her mean response curve that explains how the sIBDQ score changes over time (intraindividual changes). A mixed effects model is used to model individual sIBDQ response curves over time.

#### Justification of Sample Size

The difference in sIBDQ scores from baseline to week 10 (week 52 and week 104) will be analyzed. The null hypothesis is that the average difference is zero. The alternative hypothesis is that the average difference has a nonzero value. Based on the results of a previous study [15], we aim to demonstrate a difference of 7 points or more with an α of .05, assuming an SD of 12, and assuming that each pair of measurements on the same individual correlates with approximately 0.5. With a sample size of 250 subjects, a power of >90% is achieved to detect the above mean of paired differences with a 2-tailed paired *t* test [16].

#### Exploratory Data Analysis

As an exploratory data analysis, correlations between the pMayo and exercise data and psychomotor data (such as sleep quality, stress, and fatigue) will be calculated.

### Definition of the Study Population

This prospective observational investigator-initiated trial will be conducted with 250 participants at approximately 50 sites all over Germany. The gender ratio will be balanced.

### Selection of Study Sites

Sites are IBD-experienced hospitals or gastroenterology practices in Germany. Site selection will be made by the study investigators. By signing the investigator agreement, each site confirms its fulfillment of all formal requirements for inclusion in the study and guarantees its compliance with data privacy laws and any other regulations about the execution of this observational study.

### Participant Criteria

The inclusion criteria for the FilgoColitis study include (1) the confirmed diagnosis of UC (according to the current guidelines from the German Society for Gastroenterology, Digestive and Metabolic Diseases and European Crohn’s and Colitis Organization), (2) the initiation of therapy with filgotinib at the physician’s discretion regardless of potential study participation, (3) age of the patient between 18 and 80 years at inclusion, and (4) in-label use according to filgotinib product information. The exclusion criteria include (1) planned surgical intervention with hospitalization, (2) history of malignant disease (except “nonmelanoma skin cancer”), and (3) contraindications for treatment with filgotinib (according to the product information).

### Study-Specific Examinations: The Use of Wearables

Within the scope of the additional examination, the 2 accelerometry-based wearables (SENS motion accelerometry leg sensor, and GARMIN smartwatch) will be provided by the clinical research organization. Participation in the additional examination is voluntary.

The wearables aim to improve data collection of physical activity behavior. Activity and psychomotor data are recorded by the provided trackers and transmitted to the server via the MyTARGET app.

The MyTARGET app (Figure 1) is a therapy support app for people with IBD. It was developed by the competence network IBD (Kompetenznetz Darmerkrankungen) and the German Association of Gastroenterologists (Berufsverband Niedergelassener Gastroenterologen Deutschlands) in close cooperation with experienced gastroenterologists, physician assistants, and patients to provide the best possible support for patients in their daily lives. The app is freely accessible and can be used by anyone. Within the app, there is a specific FilgoColitis study area, where only study participants have access via a QR code. In this area, patients can connect their wearables to their smartphones via Bluetooth. Once the devices are connected, a secure data transfer of the movement data to the study servers can take place assisted by the MyTARGET app. All data are stored only on the study server and are not passed on to the GARMIN company. The patients also receive a small output of their movement data.

**Figure 1 figure1:**
[figure not shown]
Homescreen and tracking area of the MyTARGET app.

The GARMIN watch may be worn for the entire study period of 24 months (day and night). If the physician and patient agree, it is desirable to be worn during the 10-week induction phase (day and night) or at least in the following 7 days after the baseline visit. For the follow-up visits, the GARMIN watch, if used, may be worn for 7 days after each follow-up visit (day and night).

If desired by the patient, the SENS motion sensor may be worn from the baseline visit and at each follow-up visit for 7 days (day and night). Both wearables may also be worn 3 days before the start of filgotinib therapy (baseline visit), if applicable. These movement data are not made available to the treating physician in a direct temporal context so as not to influence therapeutic decisions.

### Schedule of Visits

Visits at the study site are scheduled at inclusion (baseline visit week 0) and during follow-up (week 10, month 6, 12, 18, and 24). Follow-up visits are not fixed scheduled visits but are to occur when the study participant sees his or her physician as part of routine treatment.

### Documentation

Data are recorded using case report forms at the study sites and are transferred to an electronic case report form at the site. Data outlined in Table 1 are recorded during the baseline examination and at follow-up. In addition, each (serious) adverse event is recorded.

The movement data of the additional wearable examination are recorded and stored locally as soon as the patient puts them on (Textboxes 1 and 2). Data are transferred from the wearables to the MyTARGET app on the patient’s smartphone via Bluetooth. The patient is given access to the study area via an individual QR code within the app. In this QR code, a digital pseudonym is stored, which enables the assignment of the movement data to the patient’s own study number. When the wearables and app are connected via Bluetooth, the data are automatically transferred from the devices to the MyTARGET app on the study participant’s cell phone and from there to the study server (Figure 2). There, the movement data are merged with the site-based collected data on the patient’s pseudonym.

**Table 1 table1:** Clinical data collected in the FilgoColitis study stratified by baseline and follow-up visits.

Variable			Baseline visit	Follow-up visits (week 10, month 6, 12, 18, and 24)
**General information**				
	Date of patient visit		✓	✓
	FilgoColitis study number		✓	
	Diagnosis of ulcerative colitis		✓	✓
	**Study participation with wearables**		✓	✓
		GARMIN Fitness watch	✓	✓
		SENS motion ID	✓	✓
	Short pseudonym		✓	✓
**Demographic data**				
	Gender		✓	
	Date of birth		✓	✓
	Height		✓	
	Weight		✓	✓
	Waist circumference		✓	✓
	Smoking status		✓	✓
	Zip code		✓	✓
	Ethnic origin		✓	
	Social status		✓	✓
	Highest school qualification		✓	✓
	Member in the self-help organization German Crohn’s Disease and Ulcerative Colitis Association		✓	✓
	Sports activity		✓	✓
**Anamnesis**				
	Date of initial diagnosis (IBD^a^)		✓	
	First IBD symptoms (retrospective)		✓	
	Relatives with IBD		✓	
	Hospitalization		✓	✓
	Stool frequency previous night		✓	✓
	Start of filgotinib therapy (induction phase)		✓	
	Proctocolectomy		✓	✓
	Cancer diagnosis		✓	✓
	Fistula		✓	✓
	Stenosis		✓	✓
	Comorbidities		✓	✓
	Drug intolerances		✓	✓
**Current findings**				
	Montreal classification		✓	✓
	Current illness situation		✓	✓
	Laboratory parameters (C-reactive protein, fecal calprotectin, and hemoglobin)		✓	✓
	Endoscopy		✓	✓
	Extraintestinal manifestation		✓	✓
	Current medication		✓	✓
	Partial Mayo Score		✓	✓
**PROs^b^**				
	General quality of life (EQ-5D-5L)		✓	✓
	Disease-specific quality of life (sIBDQ^c^)		✓	✓
	Fatigue Questionnaire (IBD-F^d^)		✓	✓

^a^IBD: inflammatory bowel disease.

^b^PRO: patient-reported outcome.

^c^sIBDQ: Short Inflammatory Bowel Disease Questionnaire.

^d^IBD-F: Inflammatory Bowel Disease-Fatigue.

Collected data from the wearable GARMIN vívosmart 4 within the additional examination.StepsHeart rateStressRecoveryLow stressMedium stressHigh stressSleep durationSleep levelLight sleepDeep sleepRapid eye movement (REM) sleep

Collected data from the wearable SENS motion within the additional examination. Duration and steps were collected for each movement type.Lying or sitting restLying or sitting movementStandingSporadic walkingWalkingModerate intensityHigh intensityCycling

**Figure 2 figure2:**
[figure not shown]
Transfer of the movement data from wearables to the study server. eCRF: electronic case report form.

### Patient Identification

All patient data are pseudonymized. Each patient will be identified by a patient identification number assigned at each study site. The investigator will keep a patient identification list, documenting the patient identification number with the patient’s full name, date of birth, sex, and date of informed consent.

The patient identification list is part of the investigator’s file and will remain at the site. The patient identification number comprises a 3-digit clinic number and a consecutive 3-digit number of recruited patients per study site.

### Study

#### Start of Patient Participation

Any patient who meets the inclusion and exclusion criteria of the study is a potential candidate. All potential candidates who come to the attention of the investigator will be consecutively informed of the opportunity to participate in the study. Written informed consent will be obtained before the commencement of documentation.

#### End of Patient Participation

The observation of each patient ends according to the schedule with the last study visit (month 24), after 2 years. A patient’s participation in the study will be terminated prematurely if at least one of the following criteria is met: (1) withdrawal of informed consent or death of the patient, (2) change of diagnosis, (3) lack of medical justification for further participation in the study, (4) premature termination of the complete study, or (5) subsequent discovery that not all inclusion criteria are met or that any exclusion criteria are met at baseline. A change in therapy does not result in study dropout. Furthermore, patients may be declared as lost-to-follow-up if they are no longer available and thus could not be documented at more than 2 consecutive visits.

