### Objectives

This study aims to investigate the QoL and psychosocial well-being of patients with UC on filgotinib therapy over the long-term course of different disease phases under routine conditions. Therefore, we aim to use wearables additionally and collect patient-reported outcomes (PROs) related to QoL and psychomotor profiles (fatigue and depression), including physical activity, under real-world conditions.

Using wearables, we aim to investigate whether physical activity data are related to QoL in patients with UC and whether there is an association between physical activity patterns, health status, and QoL, and additionally to define a new outcome in UC treatment. Furthermore, we will evaluate the safety profile of filgotinib therapy considering (serious) adverse events.

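### An unrestricted medical reason for ending participation could remove some treatment failures from follow-up, and the lost-to-follow-up rule cannot classify anyone last documented at month 12 or month 18

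*Protocol article*

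**What the plan says.** The Objectives section sets out to study quality of life "over the long-term course of different disease phases under routine conditions". The Schedule of Visits has a baseline visit and five visits "during follow-up (week 10, month 6, 12, 18, and 24"), and adds that "Follow-up visits are not fixed scheduled visits": they happen when the patient attends for routine care.

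End of Patient Participation states that observation "ends according to the schedule with the last study visit (month 24), after 2 years". It then lists five conditions, any one of which ends participation early. The third is "lack of medical justification for further participation in the study", with no further definition. After the list it says: "A change in therapy does not result in study dropout". Finally, "patients may be declared as lost-to-follow-up if they are no longer available" and therefore "could not be documented at more than 2 consecutive visits".

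Three other places bear on the point:
- Table 1 collects hospitalization, proctocolectomy and current medication at the follow-up visits as well as at baseline.
- The Statistics Overview analyses the sIBDQ change from baseline to week 10 (primary), week 52 and week 104 with a paired comparison. It also reports completed questionnaires at each time point as a percentage of eligible patients.
- Repeated Measurements Over Time plans a mixed effects model.

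**The concern.** The study is noninterventional, and apart from the voluntary wearable examination, taking part means being documented at routine visits. It is hard to see what would medically justify or not justify that. A site looking for a meaning may settle on the patient for whom filgotinib has not worked or has been stopped. The therapy-change sentence covers only part of that group. With about 50 sites, a non-responder, a patient who stops filgotinib without a replacement, or one who goes to surgery could be kept at one site and ended at another, and nothing in the text settles which is correct.

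Such patients may be numerous. The Background puts the effectiveness of existing targeted therapies at about 30%, Strengths and Limitations expects mainly patients in whom several biologics have failed, and 90% of the first 69 enrolled had already received biologics. If they leave, the later sIBDQ changes describe those who did well, and adverse events after the ending are not recorded.

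The lost-to-follow-up rule is a separate defect. Its threshold does not fit the number of visits left in the second year, so it cannot classify losses there.

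**Working it through.** **1. The plan's own power figure.** Inputs from Justification of Sample Size: difference 7, SD 12, correlation 0.5, two-sided alpha 0.05, N = 250.

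- SD of the difference = 12 × √(2 × (1 − 0.5)) = 12.
- Noncentrality = (7/12) × √250 = 9.22.
- Power ≈ Φ(9.22 − 1.96), which is about 1.00. The stated figure of more than 90% holds.
- From the noncentral t distribution, 33 pairs already give 90%.

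Losing patients is therefore a question of bias at the later time points, not of power.

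**2. The lost-to-follow-up rule against the schedule.** More than two consecutive visits means at least three.

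| Last documented visit | Follow-up visits left | Rule first met at |
|---|---|---|
| Baseline | 5 | Month 12 |
| Week 10 | 4 | Month 18 |
| Month 6 | 3 | Month 24 |
| Month 12 | 2 | Never |
| Month 18 | 1 | Never |

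For a patient last seen at month 6 the rule is met only at the scheduled end. Lowering the threshold to two missed visits would reach the month-12 row (at month 24) but still not the month-18 row, so a different threshold alone is not enough.

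**3. What the termination text covers.**

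| Event | Exempted after the list? | Collected at follow-up in Table 1? |
|---|---|---|
| Change of therapy | Yes | Yes (current medication) |
| Filgotinib stopped, nothing replaces it | Not stated | Yes (current medication) |
| Non-response | Not stated | Yes (partial Mayo Score, sIBDQ) |
| Hospitalization | Not stated | Yes |
| Surgery (proctocolectomy) | Not stated | Yes |

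Table 1 suggests that these patients were meant to stay. The termination text does not say so.

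**4. Possible size of the bias (assumed inputs).** The article gives no removal rate. Take a true mean change of 7 in all patients, a removed fraction d with mean change m, and an analysis of the remaining patients only:

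completers' mean = (7 − d × m)/(1 − d); 95% CI half-width = 1.96 × 12/√(250 × (1 − d)).

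| d | Mean if m = 0 (shift) | Mean if m = 3 (shift) | Half-width |
|---|---|---|---|
| 10% | 7.78 (0.78) | 7.44 (0.44) | 1.57 |
| 20% | 8.75 (1.75) | 8.00 (1.00) | 1.66 |
| 30% | 10.00 (3.00) | 8.71 (1.71) | 1.78 |
| 40% | 11.67 (4.67) | 9.67 (2.67) | 1.92 |

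The shift exceeds the half-width from 20% removal if m = 0, but among these values only at 40% if m = 3.

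**5. The completion percentage.** Suppose, again as an assumption, that 20% of 250 are terminated and everyone else completes. With all enrolled patients as denominator, completion is 200/250 = 80%. If terminated patients no longer count as eligible, it is 200/200 = 100%. The article does not say which applies.

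**The case against.** A reader might infer that the protocol lets sites drop treatment failures at will, that the two-year result is therefore selected, and that its attrition is hidden. The documents do not support any of these.

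- **Removal of failures is not a stated rule.** The exemption bars dropout for a therapy change, so a site that ended documentation because filgotinib was replaced would act against the text. This stands. The gap is limited to failures that are not therapy changes. One could argue that stopping filgotinib is itself a change in therapy, but the text does not say so.
- **Participation is more than documentation.** The wearables are study-specific, and 80% of the first patients accepted them. This stands in part. The examination is voluntary, however, so ending it need not end follow-up.
- **Attrition is not hidden.** Completion percentages are promised at each time point, so missing questionnaires at months 18 and 24 will show. This stands, except that the denominator is undefined.
- **The lost-to-follow-up label is optional and deletes no data.** With visits tied to routine care, some tolerance of missed visits is reasonable. This stands, and it keeps the defect to one of classification. Nor would a working rule reveal endings under the third criterion, which are terminations. The two defects are separate.
- **The mixed effects model uses scores recorded before removal.** This helps where removal follows recorded worsening. It does not help where the deterioration came after the last recorded score, and the paired analyses need both scores.
- **The full protocol may define the criterion.** That is possible, as it is not shown. As published, the criterion is mandatory and unrestricted.

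**Conclusion.** The point holds as a risk created by loose wording plus a rule that does not fit its schedule. The lost-to-follow-up defect follows from counting visits and needs no assumption: nobody last documented at month 12 or 18 can be classed as lost. The risk from the third criterion rests on two things the article does not settle: whether sites would apply it to non-response, stopping without replacement, hospitalization or surgery, and how often.

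If they did, the month-12 and month-24 changes could be biased upward and later adverse events lost. The shifts of 0.44 to 4.67 points come from assumed removal rates and assumed changes in those removed. They show what is possible and do not estimate this study. It is not established that the two-year result is selected. The week-10 primary end point is little affected, and power is not in question. The change is worth making because it is cheap and protects the long-term objective.

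**What to change.** 1. Delete the third criterion or restrict it to administrative reasons. State that non-response, stopping or changing filgotinib, hospitalization or surgery does not end documentation. This concerns data collection only, not treatment.
2. Replace the lost-to-follow-up rule with an end-of-study status: a patient with no month-24 documentation and no withdrawal, death or other recorded ending is lost from the last documented visit.
3. Use all enrolled patients still alive as the denominator for the completion percentages.
4. Report premature endings by reason.

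The cost is a short amendment, a letter to sites, slightly more documentation, and possibly one form field for the reason for ending, which Table 1 does not list. The reported loss rate will look higher, and some patients who merely missed the last routine visit will count as lost. Reporting the last documented visit alongside makes that visible.

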#### Study Duration

This prospective study is planned for over 3.5 years (including 18 months of recruitment and 24 months of follow-up documentation per patient). The complete study is considered to have ended after all queries from the study coordination center have been answered by each study site, at the latest, 2 months after the last visit of the last patient.

#### Data Quality, Quality Control, and Assurance

The input fields in the web-based documentation form are stored with an input logic to avoid incorrect entries. In addition, remote monitoring of the data is permanently carried out and, if necessary, corresponding queries are made. Approximately 30% (n=75) of documented cases will be reviewed via in-house or on-site monitoring. Within the on-site monitoring, all study-relevant documents will be inspected and checked for completeness and current validity. In case of missing or implausible data, queries are generated and forwarded to the corresponding study site. This process is described in more detail in the monitoring manual.

#### Data Collection

Data collection of questionnaires (clinical data) and wearables data will take place on secured web servers based in Germany. The data will be transmitted and evaluated pseudonymously.

### Ethics Approval and Regulatory Aspects

The principal investigators and CED Service GmbH in Kiel are responsible for obtaining the required ethics committee approval as well as compliance with data protection regulations. Approval is obtained from the ethics committee of the medical faculty of the University of Kiel (D 609/21). The German Federal Institute for Drugs and Medical Devices (Bundesinstitut für Arzneimittel und Medizinprodukte), the “Kassenärztliche Bundesvereinigung,” the “Spitzenverbände der Krankenkassen,” and the “Verband der Privaten Krankenversicherungen e.V.” have been notified of this noninterventional study according to §67 of the German Medicinal Products Act (Arzneimittelgesetz). A final report will be sent to the responsible federal authority after completion of the data collection according to §67 (6) of the German Medicinal Products Act. Furthermore, the study is published in the public German Clinical Trials Register (DRKS00027327).

Before enrollment in the study, the investigator will inform each patient of the nature, significance, risks, and scope of the study and the patient’s right to withdraw from the study at any time without prejudice. The patient will be given an informed consent form describing the study in nonscientific and generally understandable language. Each patient must consent in writing to participate in the study. The patient must be given sufficient time to decide and ask questions before signing the consent form.

## Results

The enrollment commenced in December 2021 and was still open at the date of submission. The study is expected to complete in June 2026. After 6 months of study initiation, 69 patients were enrolled in FilgoColitis. The median age of patients is currently 41.7 (IQR 28.7-56.0) years; 52% (n=36) of patients were male and had a disease duration of 7.4 (IQR 4.3-14.8) years. In total, 90% (n=62) and 23% (n=16) of patients were pretreated with biologics and small molecules, respectively. Wearables were accepted by 80% (n=55) of patients.

## Discussion

### The Rationale for the Study

Treatment of moderate to severe UC remains challenging with approximately 30% of patients benefiting from biologics. Further modes of action are therefore needed. JAK inhibitors play a role by inhibiting the Janus kinase/signal transducers and activators of transcription pathway, thereby slowing down the inflammatory process [17].

The first to market in 2019 was a pan JAK inhibitor, tofacitinib. It is hoped to achieve a more specific effect by inhibiting individual JAKs in a more targeted manner: filgotinib is a JAK1 preferential inhibitor, and therefore fewer side effects are expected.

The pivotal SELECTION study [18] showed significantly higher efficacy (clinical remission) in patients receiving 200 mg filgotinib therapy when compared to a placebo in both the induction and maintenance phases. The incidence of serious adverse events was not higher in the filgotinib groups compared to the placebo group.

The safety profile and the effectiveness of objective disease scores as well as PROs under real-world conditions have not yet been studied. Therefore, the FilgoColitis study was initiated shortly after approval in Germany and Europe. The study focuses on PROs, which will be collected both subjectively via questionnaires but also using wearables to provide objective data on activity behavior and psychomotricity. In addition to abdominal pain, fatigue is reported by many patients as a common complication [12]. Therefore, the IBD-F is applied, for which the German version has recently been validated [14]. The scale of the IBD-F questionnaire was developed to be used in the diagnosis of fatigue or to monitor fatigue levels over time. The IBD-F scale consists of 3 sections: section I identifies the level and duration of fatigue, section II assesses the impact of fatigue on daily activities, and section III identifies causes and other factors related to fatigue. The FilgoColitis study will analyze if there is a correlation between the objective movement measures, disease activity, and fatigue.

